### Recruitment and randomisation

The flow of participants through the study will reflect the recommendations from the Consolidated Standards of Reporting Trials statement [31] and is outlined in Figure 1. Participants will be identified at their regular outpatient clinic appointments to the Departments of Respiratory and Sleep Medicine at Alfred Health, Austin Health and Western Health. Eligible participants will be approached by the researchers who will explain the study. Participants will receive written and verbal information about the study and written consent will be obtained from all participants. The Human Research Ethics Committees of Alfred Health, Austin Health, Western Health and La Trobe University approved the study. The study protocol has been registered with the Australian New Zealand Clinical Trials Registry (ACTRN12611000416998).

**Figure 1 F1:**
[figure not shown]
Flow of patients through the study.

Randomisation will be stratified according to the three subgroups IPF, dust-related ILD and connective tissue disease-related ILD. This will ensure that all subgroups of ILD are evenly distributed between the intervention and control groups. The randomisation will also be stratified for disease severity according to TLCO <or ≥40% to ensure that those with severe disease are evenly distributed between the intervention and control groups. A set of permuted blocks will be generated for each of the following subgroups: dust-related ILD, connective tissue disease-related ILD, IPF with TLCO < 40% and IPF with TLCO ≥ 40%. The random allocation sequence will be generated using a computer generated random number list. Concealment of group allocation will be achieved by giving the responsibility for allocation sequence generation and group allocation to a researcher independent of the study and its investigators. The group allocation will be kept in sealed, opaque envelopes in a central location. Following the baseline assessment, participants will be randomly allocated to either the exercise training group or to a control group by a researcher, who is not involved in the recruitment or assessment of the participants or the execution of the intervention, by opening the sealed opaque envelope.

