### Sample size

One hundred and sixteen participants will be required to detect a significant difference in the primary outcome measure of change in functional exercise capacity (6-minute walk distance [6MWD]). This is based on the 80% probability of detecting a difference in the change in 6MWD between the intervention and control group using data from our previous randomised control trial [17] and Cochrane review [24]. Our sample size calculation of 116 has been powered to include the required number of participants in the three most commonly observed ILD subgroups: IPF, dust-related ILD and connective tissue disease-related ILD. To detect a true difference in the change in 6MWD in subjects with IPF, a total of 72 subjects, 36 in each group, is required. This is based on the lower limit of the range for the minimal important difference (MID) of 29m [30] with a standard deviation (SD) of 43m. To detect a true difference in the change in 6MWD between groups using the upper limit of the MID of 34m [30] with SD 43m, a total of 54 subjects, 27 in each group, would be required. In subjects with dust-related ILD, a total of 22 subjects, 11 in each group, is required. This assumes that the true difference between groups is 52m with SD of 40m. In subjects with connective tissue disease-related ILD, 22 subjects, 11 in each group, is required, assuming a difference of 38m with SD 30m.

Data from our previous study [28] indicate that to detect a relationship between carbon monoxide transfer factor (TLCO) and change in 6MWD following pulmonary rehabilitation with 80% power will require 31 subjects in the pulmonary rehabilitation group. This assumes that the true change in 6MWD is 15 meters for each 10% change in baseline percent predicted TLCO. To detect a relationship between degree of pulmonary hypertension and change in 6MWD with 80% power will require 35 subjects in the pulmonary rehabilitation group. This assumes that the true change in 6MWD is 17 meters for each 10mmHg change in baseline right ventricular systolic pressure.

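### Stratification by TLCO is stated for the whole randomisation, but the listed block sets apply it only within IPF, so balance on severity is not ensured by design for 44 of the 116 planned patients

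*Protocol article*

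**What the plan says.** The text is in the protocol article, Recruitment and randomisation, in the paragraph below Figure 1.

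- Aetiology: "Randomisation will be stratified according to the three subgroups IPF, dust-related ILD and connective tissue disease-related ILD".
- Severity, in the same paragraph: "The randomisation will also be stratified for disease severity according to TLCO <or ≥40% to ensure that those with severe disease are evenly distributed". The sentence carries no restriction to one aetiology.
- Operational rule, immediately afterwards: one set of permuted blocks for each of "dust-related ILD, connective tissue disease-related ILD, IPF with TLCO < 40% and IPF with TLCO ≥ 40" per cent.

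The Sample size section fixes how many patients fall in each set. It says "Our sample size calculation of 116 has been powered to include the required number of participants in the three most commonly observed ILD subgroups". For IPF, "in subjects with IPF, a total of 72 subjects, 36 in each group, is required". It then says "In subjects with dust-related ILD, a total of 22 subjects, 11 in each group, is required", and it gives the same size, 11 per group, for connective tissue disease-related ILD.

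**The concern.** The severity sentence describes a property of the whole trial, and the block list delivers it only in IPF. The part left out is the two smallest subgroups. Each is planned at 11 per arm and has its own planned subgroup analysis, so chance differences in severity between arms are proportionally largest there.

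Severity is central to the trial's question. The Background hypothesises that training works regardless of severity outside IPF, and that in IPF it works best in milder disease. A reader who stops at the severity sentence would believe that severe disease is balanced by design in every subgroup, and a trial report could repeat that. What is at stake is an accurate account of the design and some avoidable noise in two subgroup contrasts. The validity of the trial is not at stake.

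**Working it through.** **1. Subgroup sizes, reproduced first.** Inputs come from the Sample size section: 80% power; IPF 29 m with SD 43 m; dust-related 52 m with SD 40 m; connective tissue 38 m with SD 30 m. Alpha is not stated, so two-sided 5% is assumed. The normal approximation is n per group = 2 × (1.960 + 0.842)² × (SD/difference)² = 15.70 × (SD/difference)².

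| Subgroup | Normal approximation | Rounded up | t-test | Rounded up | Article |
|---|---|---|---|---|---|
| IPF | 15.70 × (43/29)² = 34.5 | 35 | 35.5 | 36 | 36 |
| Dust-related | 15.70 × (40/52)² = 9.3 | 10 | 10.3 | 11 | 11 |
| Connective tissue | 15.70 × (30/38)² = 9.8 | 10 | 10.8 | 11 | 11 |

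The t-test version matches exactly, and 72 + 22 + 22 = 116.

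**2. Claimed against listed strata.** Three aetiologies crossed with two TLCO levels need 3 × 2 = 6 block sets. The article lists 4. The two missing splits are in dust-related and connective tissue disease-related ILD, which hold 22 + 22 = 44 patients; 44/116 = 37.9%.

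**3. Possible chance imbalance in one subgroup of 22.** The share with TLCO below 40% outside IPF is not given, so it is varied. With 11:11 allocation and K severe patients, the number X in one arm is hypergeometric (22, K, 11). The difference between arms is 2X − K.

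| K severe of 22 | P(difference of 3 or more) |
|---|---|
| 4 | 9% |
| 5 | 31% |
| 6 | 15% |
| 7 | 36% |
| 8 | 18% |
| 9 | 39% |
| 10 | 20% |
| 11 | 39% |
| 12 | 20% |

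The values alternate because the difference has the same parity as K. For even K, a difference of 3 or more means 4 or more.

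**4. Possible shift in a subgroup contrast.** The Sample size section assumes 15 m per 10% of predicted TLCO, or 1.5 m per point, and needs 31 patients in the rehabilitation group. The TLCO SD is not given and has to be inferred. With a Fisher z approximation, z = 2.80/√28 = 0.529, so r = 0.485, and the TLCO SD = r × (outcome SD)/1.5. Outcome SDs of 30, 40 and 43 m give 9.7, 12.9 and 13.9 points. About 13 is used here.

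- Standard error of the between-arm difference in mean TLCO: 13 × √(2/11) = 5.5 points.
- Same slope in both arms: 1.5 × 5.5 = about 8 m.
- Slope in the training arm only: about half of that, 4 m, because the imbalance is split around the common mean.
- Slope zero outside IPF, as hypothesised: 0 m.

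For comparison, the standard errors of the contrasts themselves are 40 × √(2/11) = 17 m (dust-related) and 30 × √(2/11) = 13 m (connective tissue).

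**The case against.** The strongest reply is that the operative rule is not in doubt. The block list follows at once, so whoever generates the lists has a single specification, and allocation under it is valid. The IPF-only split also fits the trial's rationale. The Background reports an earlier uncontrolled study in which severity was related to response in IPF and not in other ILDs, and strata of 22 are small to divide further. This stands. It explains the four lists, but it also means that the general severity sentence is the one that is wrong.

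A second reply is that covariates for the mixed model are commonly left to the analysis plan, which is not shown. That stands too: the absence of TLCO from the model described under Statistical analysis is not counted as an error here. The covariate is proposed only as a remedy.

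A reader might go further and infer that the dust-related and connective tissue comparisons are biased, or that the primary result is compromised. The documents do not support this. Randomisation balances severity in expectation, and variation due to TLCO is already part of the outcome SDs of 40 m and 30 m. Nor should 39% or 8 m be taken as the expected size. The first lies at the top of a range that depends on an unknown share. The second applies a slope given only for the rehabilitation group to both arms, and to patients in whom the earlier study did not see the relationship.

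**Conclusion.** The inconsistency is real and minor. As written, severity balance is promised for all patients and ensured by design only for the planned 72 with IPF, leaving 44 of 116 outside it. Those are planned numbers, and the actual count will depend on recruitment. The sample size and the validity of the primary comparison do not change.

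The practical effect is confined to precision and chance balance in two subgroup analyses. The chance of a difference of 3 or more severe patients is about 9% to 39% per subgroup, assuming 4 to 12 severe of 22 and 11:11 allocation. A one-standard-error TLCO imbalance would move a contrast by nothing under the trial's own hypothesis. If the stated slope applied outside IPF, it would move it by about 4 to 8 m, given a TLCO SD near 13 points. The assumed effects are 38 m and 52 m. The contradiction in the text does not depend on any of these assumptions.

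**What to change.** Reword the severity sentence so that stratification by TLCO applies within IPF only, matching the four block sets. Include baseline TLCO and the aetiology strata as covariates in the between-group 6MWD model, and baseline TLCO in the dust-related and connective tissue subgroup models.

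The cost is one sentence and a covariate that the article already collects at baseline (Classification of disease severity). The downside is one degree of freedom in each of two subgroups of 22. Adding TLCO splits in those two subgroups is not needed; with strata this small it would be a trade-off rather than a correction. The sample size stays at 116.

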### Intervention

#### Exercise training group

The exercise training group will undergo a twice-weekly supervised exercise training program at the institution where they were recruited for a period of 8 weeks. The exercise program will follow the pulmonary rehabilitation guidelines for exercise prescription in chronic lung disease [32]. Each session will consist of 30 minutes of aerobic exercise plus upper and lower limb resistance training exercises. The aerobic exercise component will comprise of 15 minutes each of stationary cycling and walking, either on the treadmill or along a corridor. The initial walking intensity will be set at a speed that is 80% of the peak walking speed (km/hr) achieved on the 6-minute walk test (6MWT). The initial intensity of the stationary cycling will be prescribed at 70% of their maximum work rate estimated from their 6MWT [33] and will be adjusted to elicit a rating of perceived exertion (RPE) of 12–14 on the 6–20 Borg scale and a dyspnoea score of 3–4 on the modified Borg scale [34]. The duration of exercise on each modality will be adjusted if the participant has a co-morbidity that limits their capability on one specific modality, however the total exercise time will remain at 30 minutes. Interval training will be used for those participants who are unable to tolerate continuous exercise. The resistance program will comprise three lower limb and four upper limb dumbbell exercises. The initial load will correspond to 10-12RM (repetition maximum), that is, a weight that can be lifted correctly and comfortably at least 10 times, but not more than 12 times and elicits a RPE of 12–14 on the 6–20 Borg scale [35,36]. All exercise modalities will be progressed regularly by an experienced exercise physiologist or physiotherapist to maintain dyspnoea and fatigue scores of 3–4 and a RPE score of 12–14. Supplemental oxygen will be provided during training if SpO_2_ on room air is <88% whilst exercising and will be titrated to maintain a SpO_2_ ≥90%.

Once the participant is safely established on a supervised exercise regimen, an unsupervised home exercise program will be prescribed as per current Pulmonary Rehabilitation guidelines [37] to achieve three additional home-based exercise sessions per week. Participants will be educated on how to monitor their symptoms and their level of exertion at home and will be instructed to exercise at an intensity similar to that achieved in the supervised sessions. Participants will record their exercise session in an exercise diary and this diary will be reviewed weekly by the supervising clinician. At the conclusion of the 8-week program, participants will be instructed to continue with their home exercise program four to five times per week thereafter [32,38,39]. Attendance at 12 out of 16 sessions will be considered completion of the intervention.

#### Usual care group

Participants randomised to the usual care group will not undergo any supervised exercise training and will not receive any recommendations regarding exercise training or physical activity. These participants will be contacted once weekly by telephone for the duration of the 8 week intervention period to provide general support and health advice and to answer any queries or concerns the participants may have. These phone calls will be conducted according to a standardised script. This is a commonly used control for exercise training interventions and was used in our earlier randomised controlled trial in ILD [17]. The participants in the usual care group will be offered exercise training at the conclusion of the 6 month follow-up period.

#### Outcome measures

Outcome measures will be collected at baseline, upon completion of the intervention period (nine weeks) and at six months following completion of the intervention (Figure 1). A six month follow-up period is the longest we consider to be clinically feasible without excessive loss of participants due to clinical decline and death. At baseline, data collection will include age, gender, body mass index, past medical history, smoking history, use of oxygen therapy, current pharmological treatment and all of the following outcome measures.

#### Primary outcome measure

1. Change in functional exercise capacity will be measured with 6MWT according to standardised criteria [40]. Two tests will be conducted separated by a 30-minute rest period and the best result recorded. Supplemental oxygen will be used during both 6MWTs in participants who already have exertional oxygen or for those who have resting SpO_2_ <88%. Supplemental oxygen will be used at a flow rate of 4L.min^-1^ for the second test if SpO_2_ <85% during the first 6MWT [41-43]. Follow up tests will be conducted on the same oxygen flow rate. The primary outcome is change in 6MWD from baseline to nine weeks. Six-minute walk distance has been shown to correlate strongly with maximum exercise capacity (VO_2_peak) in IPF and has shown responsiveness to change following pulmonary rehabilitation in IPF [18] and ILD [17].

#### Secondary outcome measures

1. Peripheral muscle strength will be assessed using a hand held dynamometer (Commander Power track II, JTech Medical, Utah, USA). Three maximal isometric contractions of the elbow flexors and knee extensors on the dominant side will be tested. Skeletal muscle weakness, in particular quadriceps weakness, has been shown to correlate strongly with reduced exercise tolerance and exercise capacity in patients with ILD [18,44] and was found to be an independent predictor of exercise capacity at peak exercise in patients with IPF [18]. This measure will assess the contribution of muscle strength changes to changes in exercise tolerance.

2. Health-related Quality of Life (HRQoL) will be measured using the Chronic Respiratory Disease Questionnaire (CRQ), and St George Respiratory Questionnaire idiopathic pulmonary fibrosis specific version (SGRQ-I). The CRQ has been validated previously in ILD [8] and has demonstrated improvements following exercise training in ILD [17]. The SGRQ-I is designed to be more responsive in patients with IPF than the original St George respiratory questionnaire (SGRQ) and has similar psychometric properties to the original SGRQ [45].

3. Dyspnoea will be measured using the University of California San Diego Shortness of Breath Questionnaire (UCSD SOBQ) and the Modified Medical Research Council dyspnoea scale (MMRC). The UCSD SOBQ comprises 24 items that assess dyspnoea over the preceding week and is a reliable and valid instrument used to assess dyspnoea associated with Activities of Daily Living (ADL)s in patients with chronic lung disease [46-48]. The MMRC is a valid measure of breathlessness and symptom severity in ILD [49,50].

4. Anxiety and Depression will be measured using the Hospital Anxiety and Depression Scale (HADS). The HADS has been designed to detect and measure the severity of anxiety and depression and has been shown to be a reliable instrument in evaluating anxiety and depression in IPF and ILD [51,52].

5. The Global Rating of Change Scale will be used to assess the participants’ self-perceived improvement or deterioration over time. The Global rating of change scale involves asking the participant whether there has been any change in their symptoms or walking ability since their commencement in the study [53]. Participants can answer either ‘worse’, ‘about the same’ or ‘better’. If subjects state that they are worse or better they are asked to grade how much worse or better on a Likert scale from one to seven. The global rating of change has been used to establish the minimal important difference for the 6MWD in people with ILD [30].

At 9 weeks and at 6 months follow up participants will undergo repeat measurements of the 6MWT, peripheral muscle strength, CRQ, SGRQ-I, UCSD SOBQ, MMRC, HADS and Global Rating of Change to evaluate the immediate and long term effects of exercise training. An independent assessor, blinded to group allocation, will perform all outcome assessments.

#### Classification of disease severity

1. Respiratory function testing will be performed in accordance with the American Thoracic Society guidelines [54] to quantify disease severity and to assess any clinical change in respiratory function over time. Standard spirometric measures will include forced vital capacity (FVC) and forced expiratory volume in one second (FEV_1_) and will be performed at baseline and at six months follow up. Carbon monoxide transfer factor will be measured at baseline and at six months follow up. Static lung volumes measured via plethysmography will be measured at baseline only and will include total lung capacity (TLC), functional residual capacity (FRC) and residual volume (RV).

2. Pulmonary Hypertension will be assessed by a trans-thoracic echocardiogram. Pulmonary hypertension is a common complication of ILD [4,9] and patients with concomitant pulmonary hypertension are likely to have greater exercise impairment.

The respiratory function tests and transthoracic echocardiogram will be performed by routine clinical personnel at the treating hospital and they will be unaware of the group allocation.

#### Statistical analysis

Data will be analysed using intention-to-treat principles, with inclusion of all available data regardless of whether the intervention is completed. The response of exercise training and control groups will be compared for change in exercise and HRQoL variables using linear mixed model analyses. Planned subgroup analyses will be conducted for participants with IPF, dust-related ILD and connective tissue-related ILD. Multiple regression analysis will be undertaken to establish which subjects respond best to exercise training and when this treatment should be offered, with change in 6MWD following exercise training as the dependent variable. Baseline demographic and physiological variables such as age; gender; disease aetiology; percent predicted TLC; percent predicted FVC; TLCO; pulmonary artery pressure; and the extent of oxyhaemoglobin desaturation during exercise will be used as predictors.

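### The primary comparison of change in 6MWD is stated with no baseline 6MWD or stratification term attached, which gives up a modest amount of precision at almost no saving

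*Protocol article*

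**What the plan says.** The Primary outcome measure section fixes the endpoint: "The primary outcome is change in 6MWD from baseline to nine weeks". The Statistical analysis section describes the comparison in one sentence: "The response of exercise training and control groups will be compared for change in exercise and HRQoL variables using linear mixed model analyses". It names no covariate for that model and excludes none. The section then plans subgroup analyses in the three ILD groups, and a separate multiple regression on who responds to training. Aetiology and TLCO appear among the predictors of that regression. Baseline 6MWD is named in neither place.

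On allocation, Recruitment and randomisation says "Randomisation will be stratified according to the three subgroups IPF, dust-related ILD and connective tissue disease-related ILD". It adds stratification by TLCO below or at least 40%, and then "A set of permuted blocks will be generated for each of the following subgroups": dust-related ILD, connective tissue disease (CTD)-related ILD, and IPF in two TLCO bands. So TLCO is a stratifier within IPF only.

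The Sample size section sizes each aetiology group on the between-group difference in change. For IPF, "a total of 72 subjects, 36 in each group, is required", from the "lower limit of the range for the minimal important difference (MID) of 29m [30] with a standard deviation (SD) of 43m". Dust-related ILD uses 52 m with SD 40 m, and CTD-related ILD 38 m with SD 30 m, each with 11 per group.

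**The concern.** Change in 6MWD is usually negatively correlated with its baseline. A comparison of raw change then carries variance that a baseline covariate would remove, and any chance baseline difference between the arms feeds partly into the estimate. Permuted blocks within strata force the arms to balance on aetiology and, in IPF, on TLCO. If those factors predict change and the model omits them, the standard error does not credit that balance and comes out somewhat too large.

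Precision and power are at stake, not validity. They matter because each aetiology group is sized only just above 80% power, the Sample size section states no allowance for loss, and the Outcome measures section expects some participants to be lost to clinical decline and death.

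**Working it through.** **1. The plan's own sizes.** The significance level is not stated, so two-sided 5% is assumed. Two-sample t-test on change, 80% power, 1:1:

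| Group | Difference / SD (m) | n per arm needed | Stated | Power at stated n |
|---|---|---|---|---|
| IPF | 29 / 43 | 35.5 | 36 | 80.6% |
| IPF, upper MID | 34 / 43 | 26.1 | 27 | 81.4% |
| Dust-related | 52 / 40 | 10.3 | 11 | 82.6% |
| CTD-related | 38 / 30 | 10.8 | 11 | 80.7% |

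Rounded up, these match the stated sizes, and 72 + 22 + 22 = 116. The sizes therefore rest on unadjusted change scores and do not need adjustment to reach 80%.

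**2. What baseline adjustment could add in IPF.** Let r be the correlation of change with baseline. Adjustment multiplies the residual variance by 1 − r², so the standardised difference becomes (29/43)/√(1 − r²). With equal SDs at baseline and follow-up, |r| = SD of change / (2 × SD of 6MWD). The documents give no cross-sectional SD, so 80 to 140 m is assumed:

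- SD 80 m: |r| = 43/160 = 0.27, r² = 0.07, power about 83%.
- SD 140 m: |r| = 43/280 = 0.15, r² = 0.02, power about 81%.

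At larger assumed values, |r| = 0.3, 0.4 and 0.5 remove 9%, 16% and 25% of the variance and give 84%, 87% and 90%. With an SD of change of 43 m, those values need a cross-sectional SD of only 72, 54 and 43 m (43/(2r)).

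**3. What a TLCO term could add.** The Sample size section says 31 exercise-group subjects give 80% power for the relation of TLCO to change. On the Fisher scale, z = (1.96 + 0.84)/√(31 − 3) = 0.53, so r = 0.48 and r² = 0.24. A t-based calculation gives r = 0.46 and r² = 0.21. So TLCO is assumed to explain about 22% of the variance of change in that arm. The control-arm slope is not given, and applying the figure to IPF alone is an assumption:

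- Same slope in both arms: 22% less variance, IPF power about 89%.
- No slope in controls: the common slope is halved and explains a quarter as much, 0.22/4 = 5.5%, IPF power about 83%.

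These figures are for continuous TLCO; a two-level stratum term gains less.

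**4. The small subgroups.** The formula in step 2 ignores the degree of freedom and the cost of estimating the slope. That is minor at 36 per arm but not at about 10. With 9 per arm (an assumed loss of two), simulation of a model adjusted for baseline gives:

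| | Unadjusted | r = 0.3 | r = 0.4 | r = 0.5 |
|---|---|---|---|---|
| Dust, formula | 74% | 78% | 81% | 85% |
| Dust, simulated | 74% | about 75% | about 78% | about 82% |
| CTD, formula | 71% | 75% | 79% | 83% |
| CTD, simulated | 71% | about 72% | about 76% | about 80% |

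At r = 0.2 there is no gain, or a loss of one to two points. With the assumed cross-sectional SD of 80 to 140 m, CTD has |r| = 30/280 to 30/160, or 0.11 to 0.19, which lies in that range.

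**The case against.** The strongest reply is that the article is silent, not wrong. A linear mixed model can carry baseline and strata. One that treats baseline as a visit with a common mean uses the baseline about as efficiently as ANCOVA. The full protocol or SAP may list the terms. This stands: a reader might infer that the plan rules adjustment out, and the text does not say so. The point concerns the comparison as stated, for which a better specification is available.

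Three other stronger readings also fail.

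- **That the result would be biased.** A comparison of change between randomised arms is unbiased, and ignoring balanced strata errs on the conservative side.
- **That the analysis contradicts the stratified design.** The planned subgroup analyses follow the aetiology strata. Within a subgroup aetiology is constant, and the block list splits TLCO only in IPF, so no stratum is omitted in the dust and CTD analyses. The strata argument applies to the pooled and IPF comparisons.
- **That a large gain is free everywhere.** A correlation of 0.3 to 0.5 has no support in the documents and may be optimistic. In the subgroups of 22, adjustment costs power if the correlation is weak, and adding TLCO there as well can bring power below the unadjusted level.

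**Conclusion.** The point holds as a modest improvement to the analysis, not as an error. As written, the primary comparison does not use two pieces of information that the design already supplies: baseline 6MWD and the stratification factors.

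In IPF, baseline adjustment alone is worth between less than one and about three points of power under an assumed cross-sectional SD of 80 to 140 m. It is worth about three to ten points if |r| is 0.3 to 0.5. A prognostic TLCO could add from about two to eight points on its own, depending on the unstated slope in controls. In the pooled analysis the direction is the same, but the documents give no target difference from which to size it. In the dust and CTD subgroups a gain is not assured. All power figures assume a two-sided 5% level and read the stated SDs as SDs of change.

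**What to change.** State the primary model as 6MWD (or its change) at nine weeks and six months on group, visit, group × visit, baseline 6MWD, aetiology stratum and the IPF TLCO stratum. Name the nine-week group contrast as primary. Use the same form for secondary outcomes, each with its own baseline.

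For the subgroups:
- **IPF:** adjust for baseline 6MWD and TLCO stratum.
- **Dust-related and CTD-related ILD:** adjust for baseline 6MWD only, or take the subgroup effects from the pooled model through a group × aetiology interaction.

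If the full protocol or SAP already names these terms, one sentence in the article is enough. The change needs no extra patients or measurements, and fixing it before unblinding removes later discretion over covariates. The cost is a few degrees of freedom, which is trivial in the pooled and IPF analyses but can cancel the gain in the subgroups of 22 if the baseline correlation is weak.
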